### Data collection

The parameters that are continuously monitored by the bedside monitor before, during, and after bronchoscopy examination, including vital signs, SpO_2_, and PtCO_2_, and the incidence of desaturation and bronchoscopy suspension/termination will be observed and recorded by an independent investigator. Meanwhile, the anesthesia information and procedures under bronchoscopy such as bronchoalveolar lavage, EBUS, and biopsy, as well as bleeding volume and the adverse events during the examination, will be collected. Demographic information of patients (age, gender, height, weight, BMI, race, smoking and drinking history, diagnosis, comorbidity, current medication, and reason for bronchoscopy examination) and laboratory results such as coagulation and chest CT will also be collected.

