**Methods and analysis:**

This randomized controlled trial will be implemented in four academic centers in China. Patients who have high-risk factors including hypoxemia, hypercapnia, morbid obesity, and narrow airway will be enrolled to use HFNC or COT during bronchoscopy examination. In the HFNC group, the initial gas flow will be set at 50 L/min with a fraction of inspired oxygen (F_I_O_2_) at 0.45, if the patient tolerates, the flow can be increased to 60L/min at most, while in the COT group, oxygen flow will be set at 6 L/min via a conventional nasal cannula. After 5 min pre-oxygenation, the bronchoscope will be inserted via the nasal route. Vital signs, oxygenation (SpO_2_), and transcutaneous CO_2_ (PtCO_2_) will be continuously monitored. The primary outcome is the incidence of hypoxemia, defined as SpO_2_ < 90% for 10 s during bronchoscopy examination, and secondary outcomes include the need for treatment escalation and adverse events.

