The major limitation of this study is the difficulty of excluding the impact of the length of examination and procedures on hypoxemia. Special operations under bronchoscope (such as EBUS), long operation time, or more than 3 biopsies under bronchoscope may cause hypoxia. Even though the patients will be randomized, those factors might be balanced into two groups, and the post hoc analysis will be performed, the conclusion from this study still might not apply to any specific type of procedure during bronchoscopy examination. Additionally, it is an open-label study, as the intervention (HFNC) is a unique device, which is largely different from the conventional nasal cannula, thus blinding the participants or investigators is impossible.

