## Data Availability

Data will be sourced from forced expiratory capacity test results, electronic medical records, and monitors. Data will be de-identified and entered into a secure, web-based electronic database. Only the investigators will have access to the final dataset. Individual participant data after de-identification that underlie the reports reported in this article can be obtained by contacting the corresponding author. Data will be available immediately following publication and ending in 5 years.

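### The primary desaturation event is recorded by an investigator who is independent but not stated to be blinded; where the monitors allow it, the event should be derived from SpO2 files without knowledge of arm.

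*Protocol article*

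**What the plan says.** All references are to the protocol article.

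- **Who records the event.** Data collection lists the monitored parameters together with "the incidence of desaturation and bronchoscopy suspension/termination", and says that these "will be observed and recorded by an independent investigator". By the Outcomes section, the incidence of desaturation is the primary outcome.
- **Blinding.** The Discussion states that the study is open-label. It reasons from the different appearance of the two devices to the conclusion that "blinding the participants or investigators is impossible". It makes no exception for whoever determines the endpoint.
- **The signal.** Data collection refers to "The parameters that are continuously monitored by the bedside monitor before, during, and after bronchoscopy examination", and SpO2 is among them. Data Availability says "Data will be sourced from forced expiratory capacity test results, electronic medical records, and monitors".
- **The event.** The abstract has it "defined as SpO_2_ < 90% for 10 s during bronchoscopy examination". The section on bronchoscopy and hypoxemia management uses at or below 90% for 10 s. The Outcomes section uses below 90% and gives no duration.

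**The concern.** Independent does not mean blinded. An investigator who observes the procedure would see whether the patient wears a high-flow device or a plain cannula. The displayed SpO2 is an objective number, but the event is more than the number. Someone must decide when a dip began, whether it lasted 10 s, and whether the signal was artefact. Staff respond to desaturation by jaw thrust or by pausing the examination, so some dips may end close to the 10-second limit. The three versions of the event add to the discretion.

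If borderline dips are called less readily in the HFNC arm, the difference enters the primary comparison directly and favours the trial's own hypothesis. Time to first desaturation and lowest SpO2, both secondary outcomes, come from the same observation.

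The reason given for not blinding, that the devices look different, holds for patients and operators. It does not hold for a person or program reading an SpO2 file that carries only a study number.

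**Working it through.** **1. The plan's own sample size, to fix the arm size.** Inputs from the Sample size calculation: 10% (HFNC) against 30% (COT), 80% power, alpha 0.05 (two-sided, from Statistical analysis). Equal allocation is assumed.

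n per arm = [1.960·√(2·p̄(1−p̄)) + 0.842·√(p1(1−p1) + p2(1−p2))]² / (p2−p1)², with p̄ = 0.20

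= [1.960·√0.32 + 0.842·√0.30]² / 0.04 = 61.6, so 62 per arm and 124 in total. This reproduces the stated 124. The planned enrolment of 148 is 74 per arm.

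**2. What differential calling would do.** Suppose there is no true effect and both arms have true rate p. A share s of true HFNC events is called and every COT event is called. The recorded rates are then a = s·p (HFNC) and b = p (COT). The article gives neither s nor a common null rate, so both are assumptions. I take p = 20%, the midpoint of the planned 10% and 30%, as the main case.

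Normal approximation to the rejection rate of the uncorrected chi-square test, with d = b−a and p̄ = (a+b)/2:

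- SE0 = √(2p̄(1−p̄)/n) and SE1 = √([a(1−a) + b(1−b)]/n)
- rejection rate = Φ[(d − 1.96·SE0)/SE1] + Φ[(−d − 1.96·SE0)/SE1]

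Example: n = 62, p = 20%, s = 80%, so a = 0.16, b = 0.20, d = 0.04 and p̄ = 0.18. SE0 = √(0.2952/62) = 0.0690 and SE1 = √(0.2944/62) = 0.0689. The rate is Φ(−1.382) + Φ(−2.543) = 0.0835 + 0.0055 = 0.089.

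Exact enumeration sums the two binomial probabilities over all tables with |z| > 1.96. At p = 20% it gives:

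| HFNC events missed | Recorded HFNC vs COT | 62 per arm | 74 per arm |
|---|---|---|---|
| none | 20% vs 20% | 0.047 | 0.050 |
| 10% | 18% vs 20% | 0.056 | 0.062 |
| 20% | 16% vs 20% | 0.084 | 0.098 |
| 25% | 15% vs 20% | 0.107 | 0.127 |

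Nearly all of the excess is in one direction. Between the first and last rows, false wins for HFNC go from 0.024 to 0.104 (62 per arm) and from 0.025 to 0.124 (74 per arm).

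**3. Sensitivity to the true rate** (normal approximation, 62 per arm). At p = 10%, missing 10% or 20% of HFNC events gives 5.4% or 6.7%. At p = 30% it gives 6.6% or 11.6%.

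**4. The same errors in patients.** At p = 20%, missing 25% of HFNC events is 0.05 × 62 = 3.1 to 0.05 × 74 = 3.7 patients. Missing 10% is 0.02 × 62 = 1.2 to 0.02 × 74 = 1.5 patients.

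These figures treat the final analysis as a single test and leave out the planned interim analysis.

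**The case against.** The strongest reply is that the endpoint is a displayed value set against a threshold, an independent investigator records it, and the open-label nature is disclosed. Nothing in the article shows that calling would differ by arm. This limits the severity. Truly small miscalling barely moves the error rate: missing one HFNC event in ten gives about 6%. The larger figures need one event in four to be missed in one arm and none in the other.

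A reader might infer that the event is called live by someone who sees the device. That is likely, given an open-label procedure and an investigator who observes it, but the article does not state it. It says only that the event is observed and recorded, and it also names monitors as a source.

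A reader might also infer that the monitors store a continuous SpO2 trace, so that the bias is plainly avoidable. The article says SpO2 is continuously monitored. It mentions no stored trace, export or sampling interval. If only coarse trend data can be exported, a 10-second rule could not be applied to them and the bedside log would be the better source.

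Arm-blind derivation also leaves another open-label route untouched. Staff who know the arm may intervene earlier in one group and so change the SpO2 values themselves.

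It can be said, too, that how an endpoint is extracted belongs in the full protocol or analysis plan. That answers a complaint about missing detail. It does not answer what the article does state: it assigns the recording of the primary event to an investigator and calls blinding of investigators impossible, with no exception for endpoint derivation.

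**Conclusion.** The point holds as an improvement that should be made if it is feasible. The primary event is assigned to an investigator not described as blinded. The stated reason against blinding does not reach endpoint derivation, and the article's own data sources suggest a better method.

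Its size is modest and conditional. At a 20% true rate and 62 to 74 per arm, missing 10%, 20% or 25% of HFNC events alone takes two-sided rejection from about 5% to about 6%, 8-10% or 11-13%. This rests on assumed, one-sided miscalling, an assumed common event rate and equal allocation. The article gives no evidence on how often, or in which direction, events would be miscalled. It does not support a claim that the primary result will be biased, or that all open-label bias can be avoided.

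**What to change.** 1. Before enrolment, confirm whether the monitors at all four hospitals can export SpO2, and at an interval fine enough to resolve 10 s.
2. Reconcile the event definitions in the abstract, the hypoxemia management section and the Outcomes section, so that one threshold and one duration rule apply to the primary outcome.
3. Where export is adequate, derive the primary event, time to first desaturation and lowest SpO2 by that one pre-specified rule, from files labelled by study number only. Include a rule for artefact and lost signal.
4. Keep the bedside log as backup when export fails, and as a sensitivity analysis.
5. In the Discussion, limit the statement on blinding to patients and operators. Say that arm-blind derivation does not address earlier intervention by unblinded staff.

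The cost is exporting and storing the files, one short script and the artefact rule. Sample size, patient procedures and staffing do not change. Traces not saved at the time may not be recoverable, so the decision has to come before the first patient.

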### Statistical analysis

Categorical variables, including the incidence of desaturation, treatment escalation, suspension or termination of bronchoscopy, etc., will be presented as percentages and analyzed by chi-square test. Continuous variables, including the desaturation time, recovery time, the lowest SpO_2_, the highest PtCO_2_, etc., will be presented as mean ± standard derivation (SD) or median and interquartile rage (IQR) and compared by independent *t*-test or Mann Whitney test, depending on the normality of distribution, which will be tested by the Kolmogorov–Smirnov test. A two-sided *P*-value of < 0.05 will be regarded as statistically significant for all tests. Data analysis will be conducted with SPSS software (SPSS 23.0; Chicago, IL).

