### Outcomes

The primary outcome is to compare the incidence of desaturation which is defined as SpO_2_ < 90% between patients using HFNC and those using COT. The secondary outcomes include the timing of the appearance of the first desaturation (namely desaturation time), the lowest SpO_2_ and the highest PtCO_2_ during the entire bronchoscopy examination, the need for treatment escalation and airway management, the number and duration of bronchoscopy suspensions, the incidence of adverse events, and the recovery time between the two groups. A post hoc analysis will be performed to explore the risk factors of desaturations during bronchoscopy examination among high-risk patients.

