### Sample size calculation (https://clincalc.com/stats/samplesize.aspx)

This study is a superiority study. While in the study [26] with a patient population close to our study during bronchoscopy examination, the incidence of desaturation of HFNC vs COT group was 13.3 vs 33.3%, respectively. However, this previous study only included hypoxemic patients while we will enroll other types of patients, so the incidence of hypoxemia in the HFNC group in their study might be higher than the incidence in ours. Thus, we assumed that when the maximal concentration of oxygen is provided by the two assigned devices, that is, when F_I_O_2_ is set at 1.0 for HFNC and oxygen flow at 6 L/min for COT, the probability of desaturation is 10% in the HFNC group and 30% in the COT group, respectively. According to statistical calculation, the sample size should be 124, with a confidence level (α) of 95%, power (1-ß) of 80%, and margin (Δ) of 0.2. Assuming a 20% dropout rate during the study, we set the final sample size to be 148. An interim analysis will be conducted once 50% of the sample size is reached.

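### Time to first desaturation is tested as an ordinary continuous variable with no rule for patients who never desaturate, so the comparison covers only patients selected on the primary outcome

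*Protocol article*

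**What the plan says.** In the Protocol article, Outcomes lists as a secondary outcome "the timing of the appearance of the first desaturation (namely desaturation time". The term therefore means time to a first event, not how long a desaturation lasts. The section on bronchoscopy examination and hypoxemia management has this time recorded when the first desaturation occurs.

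Statistical analysis then groups it with ordinary measurements: "Continuous variables, including the desaturation time, recovery time". These are to be summarised as mean and SD or median and IQR, and "compared by independent *t*-test or Mann Whitney test, depending on the normality of distribution". The same section applies one threshold throughout: "A two-sided *P*-value of < 0.05 will be regarded as statistically significant for all tests".

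The article mentions no censoring, no Kaplan-Meier, log-rank or Cox method, and no value or rank for a patient who completes the examination without desaturating. The Sample size calculation section assumes that "the probability of desaturation is 10% in the HFNC group and 30% in the COT group", so it expects 90% of HFNC and 70% of COT patients to be in that position.

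**The concern.** A patient who never desaturates has no desaturation time. Applied as written, the t-test or Mann-Whitney test leaves that patient out. Whether a patient is left out is decided after randomisation, by the primary outcome itself, which the trial expects HFNC to change. The two subsets compared are therefore not the randomised groups, and any difference in timing between them mixes the effect of treatment with selection. The best possible result, no desaturation at all, contributes nothing.

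The direction can also turn round. If HFNC mainly prevents desaturations that would have come late, the few HFNC events that remain are the early ones. The test may then report that HFNC patients desaturate significantly sooner, although far fewer of them desaturate. That result would be published under the same 0.05 rule as every other test.

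**Working it through.** **Inputs from the article.** Desaturation 10% (HFNC) and 30% (COT); "with a confidence level (α) of 95%, power (1-ß) of 80%, and margin (Δ) of 0.2"; 124 patients before dropout and 148 after. The Discussion puts a usual examination at 10–15 min.

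**Assumptions.** 1:1 allocation (the ratio is not stated; 124 = 2 × 62 fits it), a 15 min observation window, and the event timings described below.

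**1. The plan's own figure.** Two-sided test of two proportions at 0.05, pooled variance under the null, no continuity correction:

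n per arm = [1.96 × √(2 × 0.2 × 0.8) + 0.842 × √(0.1 × 0.9 + 0.3 × 0.7)]² / 0.2² = (1.109 + 0.461)² / 0.04 ≈ 61.6, rounded up to 62.

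The total is 124, as stated. The rates and the 62 per arm are therefore a sound basis for what follows.

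**2. How many patients have a desaturation time.**
- At 62 per arm: 62 × 0.10 = 6.2 HFNC and 62 × 0.30 = 18.6 COT. Together 24.8 of 124 = 20%, so 80% have none.
- At 74 per arm (148 patients, no dropout): 7.4 and 22.2, again 20%.

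This step does not depend on when events occur.

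**3. What the planned test then reports.** Trials were simulated (4,000 per row at 62 per arm; 2,000 at 74 per arm). Mann-Whitney was run among desaturators only. For comparison, a log-rank test was run on all patients, with event-free patients censored at 15 min. The true incidence is 10% against 30% in every row.

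- *Constant hazards:* hazard = −ln(1 − p)/15, that is 0.0070 per min (HFNC) and 0.0238 per min (COT).
- *Milder late-event pattern:* 10% desaturate at 1–10 min in both arms, and a further 20% at 3–15 min on COT only.
- *HFNC prevents only late events:* 10% desaturate at 1–5 min (1–6 min in the last row) in both arms, and a further 20% at 5–15 min on COT only.

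| Assumed timing | Per arm | Mean time among desaturators, HFNC / COT (min) | Mann-Whitney significant, favours COT | Log-rank significant, all patients |
|---|---|---|---|---|
| Constant hazards | 62 | 7.4 / 7.1 | 1.6% | 82% |
| Milder late-event | 62 | 5.5 / 7.8 | 23% | 80% |
| Only late events prevented (early 1–5 min) | 62 | 3.0 / 7.7 | 72% | 77% |
| Only late events prevented (early 1–6 min) | 74 | 3.5 / 7.8 | 80% | 84% |

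The means in the last three rows can be checked by hand. In the third row, for example, COT is (10 × 3 + 20 × 10)/30 = 7.7 min. Under constant hazards, Mann-Whitney rejects in 5.3% of trials in all, about its null rate (3.7% favouring HFNC, 1.6% favouring COT), and HFNC has the shorter mean time in 43% of trials.

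**4. Is the log-rank column a gain in power?** It was compared with the chi-square test on incidence (1,500 trials per setting). Under constant hazards, log-rank gives 88.5% and chi-square 88.6% at 74 per arm, and 81.2% and 80.7% at 62 per arm. In the late-event pattern at 74 per arm they give 84% and 88%. The log-rank test largely re-detects the difference in incidence that the primary analysis already tests.

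**The case against.** Several points on the other side have force.

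- **The outcome is secondary.** The primary comparison is incidence by chi-square in all patients. It is untouched, as are the sample size and the data collected. A reader would see desaturation times beside the incidence result. This stands and limits the severity.
- **The event timings are invented.** The article gives no distribution of event times. A reader might infer from the 80% row that the planned test will usually favour the wrong arm. The documents do not support that: the row assumes that HFNC prevents every late event and no early one, with little overlap in time. Under constant hazards a significant reversal occurs in about 2% of trials. Only the range can be stated.
- **Power.** A reader might set 5% for Mann-Whitney against 82–88% for log-rank and conclude that the plan throws power away. The two tests answer different questions, and step 4 shows that log-rank roughly matches the primary chi-square. The defect is the non-randomised comparison, not lost power.
- **A rank test could include everyone** if event-free patients were given a tied best rank. That is true, so the fault is the absence of any such rule, not the impossibility of one. Entering examination length in place of a time would not help, because it treats censored times as event times.
- **A fuller analysis plan may exist.** The article does not leave this method open. It names the variable and assigns it the tests.

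The core remains: followed as written, the analysis compares only patients who had the event.

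**Conclusion.** The stated method is wrong for this outcome and should be fixed; it does not threaten the trial's main conclusion. On the article's own rates, about 80% of patients drop out of the comparison, leaving about 6 HFNC against 19 COT patients (7 against 22 at 74 per arm), selected on the primary outcome. That much needs only the 10% and 30% and equal allocation.

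How often the result would mislead depends on timings that the article does not give. Over the patterns examined, with a 15 min window, the test significantly favours COT in about 2% to 80% of trials: about 2% with constant hazards, 23% in the milder pattern, and 70–80% at the extreme, although HFNC has one third of the events. The simulations used Mann-Whitney; the t-test alternative has the same selection. Nothing here undermines the primary chi-square test, and correcting the method buys a valid comparison rather than more power than the primary already has.

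**What to change.** In Statistical analysis, take desaturation time out of the list of continuous variables and state instead that:

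- time from first scope entry to first desaturation is analysed in all randomised patients, with Kaplan-Meier curves and a log-rank test or Cox model;
- patients without desaturation are censored at the end of the examination;
- the handling of examinations terminated early for other reasons (see Termination criteria) is fixed in advance, because censoring there may be informative;
- any mean or median time among desaturators is descriptive only, without a P-value.

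The cost is wording. The article already has the time of first desaturation, the first nasal entry, the end of the examination and each interruption recorded, so no new data, patients or procedures are needed. The change should be made before any comparison by arm, including the interim analysis planned at 50% of the sample.

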### Patient and public involvement

Patients and/or the public were not involved in the study design.

## Discussion

This is the first study to compare HFNC vs COT during bronchoscopy via nasal route among high-risk patients. The benefit of using the nasal route is that it allows for better control of the bronchoscope [42]. More importantly, because the patient’s mouth is mainly closed during the examination, the placement of HFNC may help generate and maintain the positive end-expiratory pressure, resulting in better oxygenation during HFNC. Even though NIV has been shown to be more effective in improving oxygenation during bronchoscopy examination, the complications of NIV, particularly gastric overdistension, are concerning [45], since in this process the bronchoscope is inserted via the oral route. In patients who receive positive pressure ventilation with the mouth constantly open and a bronchoscope is inserted via the bite block, the closure of vocal cords and the function of swallow will be substantially affected, and the risk of aspirating gas from positive pressure ventilation might be higher than in HFNC. Therefore, although we will not compare HFNC with NIV in this study, when HFNC is placed in two prongs at the same flow with the mouse closed, the nasal route may generate positive pressure comparable to that in NIV and produce similar washing-out effects [46, 47].

We only enroll patients with high-risk factors, due to the consideration of cost-effectiveness and clinical implication. For the general patient population, the incidence of desaturation during endoscopy examinations is low. Even when hypoxemia occurs during bronchoscopy examination, most can be easily resolved by increasing oxygen flows through the conventional nasal cannula. More importantly, since a general bronchoscopy examination usually lasts 10–15 min, using a new set of HFNC circuits and nasal cannula might not be worthwhile, especially considering the high cost of HFNC, which is 200–400-fold of conventional nasal cannula. As such, using HFNC to assist bronchoscopy examination for patients with high-risk factors might be more reasonable [48].

Moreover, Riccio et al. compared nasal cannula with HFNC at similar F_I_O_2_ during colonoscopy examination in morbidly obese patients and did not find a significant difference between the two groups, which implies the F_I_O_2_ other than high-flow setting is essential to the maintenance of oxygenation during endoscopy [32]. However, Yilmazel Ucar E et al. [25] compared the use of HFNC with that of COT at the same F_I_O_2_ during the endobronchial ultrasonography (EBUS) procedure among 170 patients and found a lower incidence of desaturation with HFNC. They did not enroll any patients with high-risk factors, so the exact effect of flow settings on oxygenation during bronchoscopy for patients with high-risk factors is still unclear. More importantly, in our study, we plan to compare HFNC and COT at similar F_I_O_2_ (~ 0.45), which is the maximum F_I_O_2_ setting for the COT group. If patients in the COT group continue to desaturate, they will be switched to HFNC with F_I_O_2_ at 1.0. Advanced airways will be inserted if the oxygenation still cannot be maintained. This management of hypoxemia and the study findings have an important clinical implication, as the consequences of bronchoscopy suspension or the need to switch to a different oxygen device is more meaningful than the incidence of desaturation, which might be easily resolved by simply increasing the oxygen flow with a standard nasal cannula, especially in the studies using low flow (2–3 L/min) oxygen in the COT group [23, 24, 29].

One may concern about hypercapnia during bronchoscopy [46], due to the partial occlusion of the airway and the side effects of sedation, so our study will continuously monitor PtCO_2_ before, during, and after bronchoscopy, which is also the first clinical study reporting the effects of HFNC on PtCO_2_ during bronchoscopy examination.

The major limitation of this study is the difficulty of excluding the impact of the length of examination and procedures on hypoxemia. Special operations under bronchoscope (such as EBUS), long operation time, or more than 3 biopsies under bronchoscope may cause hypoxia. Even though the patients will be randomized, those factors might be balanced into two groups, and the post hoc analysis will be performed, the conclusion from this study still might not apply to any specific type of procedure during bronchoscopy examination. Additionally, it is an open-label study, as the intervention (HFNC) is a unique device, which is largely different from the conventional nasal cannula, thus blinding the participants or investigators is impossible.

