### Limitations

➣ The study enrolls patients with four different risk factors; the general conclusion might not apply to any specific group.➣ This study does not limit the procedures of bronchoscopy; the general conclusion might not apply to any specific procedure.➣ This study excludes critically ill patients, thus the findings may not apply to these patients

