#### Exclusion criteria

Patients will be excluded if any of the following criteria is met: (1) refuse to participate; (2) local/general anesthesia bronchoscopy or rigid endoscopy is indicated; (3) age ≥ 90 years, or < 18 years; (4) pregnancy; (5) estimated duration of bronchoscopy is less than 10 min; (6) contraindication to using HFNC, including nasopharyngeal obstruction and blockage; (7) require oxygen flow ≥ 3L/min to maintain SpO_2_ at 90–97%; (8) central airway narrowness > 80%; and (9) the patient is critically ill and unsuitable for study inclusion assessed by anesthesiologists and pulmonologists.

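### Randomization can balance the planned procedures but not the length and sampling as performed, so performance bias in the open-label primary comparison is possible and the plan describes no means of detecting it

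*Protocol article*

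**What the plan says.** The Discussion names the factors as possible causes of the primary outcome: "Special operations under bronchoscope (such as EBUS), long operation time, or more than 3 biopsies under bronchoscope may cause hypoxia". It calls them the main weakness of the trial: "The major limitation of this study is the difficulty of excluding the impact of the length of examination and procedures on hypoxemia". It then says of them: "Even though the patients will be randomized, those factors might be balanced into two groups". It adds that a post hoc analysis will follow, and concludes only that the results may not carry over to a particular type of procedure. The open-label design appears next as a separate limitation: "thus blinding the participants or investigators is impossible".

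Other sections supply the setting:

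- **Limitations:** "This study does not limit the procedures of bronchoscopy".
- **Randomization and treatment:** the envelope is opened after consent, before the examination.
- **Exclusion criteria, item 5:** patients are excluded if the "estimated duration of bronchoscopy is less than 10 min", so a judgement of length exists before allocation.
- **Bronchoscopy examination and hypoxemia management:** duration runs from first nasal entry to the end of the examination, and pulmonologists decide whether to resume after a suspension.
- **Data collection:** the data include "procedures under bronchoscopy such as bronchoalveolar lavage, EBUS, and biopsy" and the reason for bronchoscopy. Planned and performed procedures are not distinguished.
- **Statistical analysis:** the incidence of desaturation is compared by a chi-square test.

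**The concern.** Balance by randomization is a property of things that exist when the envelope is opened. A planned EBUS or a planned set of biopsies can be such a thing. The minutes actually spent and the samples actually taken cannot.

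After allocation the operator knows the device and is not restricted in what is done. An operator might take more samples under HFNC because it feels safer, or fewer under COT out of caution. By the article's own account, such a change alters the risk of hypoxia. The arms would then differ in how much was done to the patient as well as in the oxygen device, and the chi-square comparison would carry both.

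The Discussion treats the matter as one of applicability and does not link it to the lack of blinding. The post hoc analysis it offers does not repair an arm-driven difference. Adjusting for procedures performed means conditioning on something that arises after randomization and may itself depend on the arm.

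**Working it through.** **1. When each factor is settled**

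| Factor | Before the envelope | After the envelope | Balanced by randomization? |
|---|---|---|---|
| EBUS or biopsies set by the indication | Yes | – | Yes, in expectation |
| Estimated duration (exclusion item 5) | Yes | – | Yes, in expectation |
| Actual duration | – | Yes, by its definition | No |
| Sampling added or dropped during the examination | – | Yes | No |

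The Discussion sentence does not separate the first two rows from the last two.

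**2. The plan's own figure**

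Inputs from Sample size calculation and Statistical analysis: 10% against 30%, two-sided alpha 0.05, power 80%. Allocation 1:1 is assumed.

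n per arm = [1.96 × √(2 × 0.20 × 0.80) + 0.8416 × √(0.10 × 0.90 + 0.30 × 0.70)]² / 0.20² = (1.1087 + 0.4610)² / 0.04 = 61.6, so 62 per arm and 124 in total, as stated.

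**3. Illustration of size**

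The documents give no shares of extended procedures and no risk ratio for them. All of the following are assumptions: an extended procedure multiplies desaturation risk by RR = 1.5, 2 or 3; COT stays at 30%; the arms differ in the share of extended procedures by g = 5, 10 or 20 points solely because operators know the arm.

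*No device effect, fewer extended procedures under HFNC* (COT share 50%, HFNC share 50% − g):

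- r = 0.30 / (1 + 0.5 × (RR − 1))
- HFNC rate = r × (1 + (0.5 − g) × (RR − 1))
- Example, RR 2 and g 20 points: r = 0.30 / 1.5 = 0.20; HFNC = 0.20 × 1.3 = 0.26, a spurious 4 points.

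*Planned threefold device effect, more extended procedures under HFNC* (COT share 30%, HFNC share 30% + g):

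- r = 0.30 / (1 + 0.3 × (RR − 1))
- HFNC rate = (r / 3) × (1 + (0.3 + g) × (RR − 1))
- Example, RR 2 and g 20 points: r = 0.30 / 1.3 = 0.2308; HFNC = 0.0769 × 1.5 = 0.1154 instead of 0.10.

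Exact rejection probabilities of the two-sided Pearson chi-square test at 62 per arm. With no gap they are 5.0% under no effect and 81.0% under the planned effect (the normal formula gives 80.3%).

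| RR | Gap | False-positive rate | Power |
|---|---|---|---|
| 1.5 | 5 | 5.0% | 79.9% |
| 1.5 | 10 | 5.2% | 78.8% |
| 1.5 | 20 | 6.0% | 76.4% |
| 2 | 5 | 5.1% | 79.0% |
| 2 | 10 | 5.7% | 77.0% |
| 2 | 20 | 7.8% | 72.6% |
| 3 | 5 | 5.4% | 77.8% |
| 3 | 10 | 6.6% | 74.3% |
| 3 | 20 | 11.6% | 66.9% |

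The two columns are alternative scenarios with opposite directions of gap.

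**4. How many covariates the primary outcome can carry**

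Expected events at 62 per arm: 62 × 0.10 + 62 × 0.30 = 6.2 + 18.6 = 24.8, roughly 25. That supports one or two covariates, not a long list.

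**The case against.** The strongest reply has five parts.

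- **Timing is not stated.** A reader might infer that unblinded operators settle EBUS, biopsies and length after allocation. No section says so. The indication may fix EBUS and biopsies, and that part is balanced in expectation. This stands and confines the point to actual length and to departures from plan.
- **The article is condensed.** A reader might also infer that no planned procedure is recorded and that the duration estimate is discarded. The article does not say that. The case report form is not shown, and the reason for bronchoscopy is collected. This stands; the sponsor may be able to confirm that such a record exists.
- **The sentence is hedged and sits inside an admitted limitation.** True, so it is too much to say that the design relies on this balance. But the consequence drawn is applicability only, and possible bias from knowledge of the arm is not mentioned.
- **Some differences belong to the device.** If better oxygenation lets an examination run on, or desaturation causes a suspension, the comparison as randomized remains valid for the assigned strategy. This stands. Only changes made because the arm is known count as bias.
- **The size depends on the assumed gap.** At a risk ratio of 2, a gap of 5 to 10 points gives only 5.1% to 5.7% false positives and 79% to 77% power. If all 148 patients were analysed (74 per arm), the normal formula gives 79.7% power at a risk ratio of 2 and a 20-point gap. The loss persists, however: without a gap the figure would be 86.8%.

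**Conclusion.** The point holds in a limited form. The Discussion's expectation of balance is sound for procedures planned before allocation and unsound for length and sampling as performed. Because the trial is open-label and procedures are unrestricted, performance bias in the primary comparison is possible.

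Its size and direction cannot be found from the documents. Under the assumed risk ratios and gaps, the effect runs from negligible (5.0% false positives, about 80% power) to material (11.6%, or 67% power). These figures rest on assumptions and do not predict what will happen. The documents do not support a claim that the primary comparison is biased.

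The reason to act is that a record of intent made before allocation is cheap and cannot be recreated without bias afterwards.

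**What to change.** 1. Before the envelope is opened, enter on the case report form the planned procedures (EBUS, lavage, biopsy and planned number) and the estimated duration already judged for exclusion item 5. If the form already holds these, say so in the protocol.
2. Leave operators free to depart from the plan for clinical reasons, and record each departure with its reason.
3. Tabulate planned against performed procedures and duration by arm, as a check for performance bias. The reasons help to separate device-driven departures from those made because the arm was known.
4. Pre-specify an adjusted analysis of the primary outcome with one or two planned items, for example planned EBUS or more than three planned biopsies. Never use performed items. The purpose is precision; this does not remove the bias.
5. Reword the Discussion to say that randomization balances planned procedures in expectation but not length or procedures as performed, and name performance bias beside the open-label limitation.

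Cost: a few form fields, about a minute of operator time per patient, and one table. No extra patients or procedures are needed.
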